## Abstract

**Background:**

Transcutaneous auricular vagus nerve stimulation (taVNS) is a non-invasive neuromodulation technique. Several studies have reported the effectiveness of taVNS in patients with disorders of consciousness (DOC); however, differences in the modulation paradigm have led to inconsistent treatment outcomes.

**Methods/design:**

This prospective exploratory trial will include 15 patients with a minimally conscious state (MCS) recruited according to the coma recovery scale-revised (CRS-R). Each patient will receive 5 different frequencies of taVNS (1, 10, 25, 50, and 100 Hz); sham stimulation will be used as a blank control. The order of stimulation will be randomized, and the patients’ CRS-R scores and resting electroencephalography (EEG) before and after stimulation will be recorded.

**Discussion:**

The overall study of taVNS used in treating patients with DOC is still in the preliminary stage of exploration. Through this experiment, we aim to explore the optimal stimulation frequency parameters of taVNS for the treatment of DOC patients. Furthermore, we expect to achieve a stable improvement of consciousness in DOC patients by continuously optimizing the neuromodulation paradigm of taVNS for the treatment of DOC patients.

**Clinical trial registration:**

https://www.chictr.org.cn/index.aspx, identifier ChiCTR 2200063828.

In their study, Hakon et al. (2020) treated 5 patients diagnosed with VS or MCS with taVNS for 8 weeks and found improvement in consciousness in 3 out of the 5 patients, with 2 patients progressing from VS and MCS to eMCS and 1 patient progressing from VS to MCS. In another study, 14 DOC patients (VS = 6, MCS = 8) received taVNS in the left ear for only 4 weeks. One of the MCS patients showed new signs of consciousness at the end of the 4-week stimulation, and the other four showed new signs of consciousness at the 4-week follow-up time point (Noé et al., 2020).

In the above study, only one patient experienced intermittent ear pruritus during stimulation; however, no significant relationship with taVNS was found, indicating that taVNS is a feasible and safe treatment for patients with DOC.

Although taVNS has shown positive results in studies of DOC, the overall effectiveness rate is low, and an understanding of the mechanisms of consciousness regulation is lacking. A growing body of evidence suggests that the optimal frequency of taVNS may vary across disorders. E.g., a clinical study of taVNS in therapeutic epilepsy showed that patients in the 25-Hz group had significantly lower seizure frequency compared to the 1-Hz group (Schnakers et al., 2008). In another clinical study of migraine patients, researchers found that although both 1 and 25 Hz taVNS improved the prognosis of patients with chronic migraine, a greater improvement was observed with 1 Hz taVNS (Schnakers et al., 2009). In their vagal cortical pathway model, Briand et al. (2020) suggested that brainstem activation may be critical for taVNS to lead to recovery of consciousness in patients with DOC. Several researchers evaluated brainstem fMRI responses to 2, 10, 25, and 100 Hz taVNS in healthy subjects and found that 100 Hz stimulation elicited the strongest brainstem response (Sclocco et al., 2020). Therefore, exploring the optimal stimulation frequency parameters for taVNS-treated should be addressed in order to improve the therapeutic efficacy of taVNS in patients with DOC.

We propose to preliminarily evaluate the optimal stimulation frequency parameters in patients with DOC treated with taVNS by changes in CRS-R and EEG before and after taVNS. The behavioral changes induced by taVNS can be measured by CRS-R, while changes in brain function brought about by taVNS can be measured by EEG. Based on previous studies, we believe that the increase in spectral power in the alpha and theta bands may represent an improvement in patient awareness (King et al., 2013; Chennu et al., 2014; Sitt et al., 2014). However, due to the small number of relevant studies, we mainly considered these two indicators but were not limited to them. Our previous study found that EEG changes were more pronounced in MCS patients than in VS patients before and after taVNS treatment (Yifei et al., 2022).

In this study, we will record the CRS-R scores and resting EEG of 15 MCS patients before and after five random taVNS at different frequencies (1, 10, 25, 50, and 100 Hz) and one sham stimulation. Changes in CRS-R scores will be used as the primary evaluation index, and the immediate effects of EEG will be used as a secondary index to assess the effects of different frequencies of taVNS on MCS patients. In this way, we will attempt to initially explore the optimal stimulation frequency parameters for taVNS treatment of DOC patients to optimize the neuromodulation paradigm and improve efficacy.

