### Procedures

The pilot study will begin as early as day 30 after the patient’s injury and will be completed within 1 year of the injury. Written informed consent will be obtained from the patient’s legal representative following an open discussion of the study objectives, methods, and potential risks. The patient’s legal representative will be informed that the patient’s legal representative has the right to ask the patient to withdraw from the study at any time during the course of the study and that each party will retain a copy of the signed informed consent form.

This is a prospective exploratory trial including 15 MCS patients, each receiving a total of five different frequencies of taVNS (1, 10, 25, 50, and 100 Hz) and a sham stimulus as a blank control for 20 min, where the order of stimulation is completely randomized. We chose these five frequencies to span the range used in previous taVNS studies, including our own. Patient’s CRS-R scores will be recorded before and after each stimulation. Each CRS-R score will be performed by no fewer than two physicians with extensive clinical experience. Also, by using a bedside 32-channel EEG (Nicolet EEG V32, Natus Neurology, USA), a 10-min resting EEG will be recorded before and after each stimulation, respectively. The interval between stimulations will be at least 48 h. SDZ-IIB electronic stimulator (Suzhou Medical Supplies Factory) will be used to provide stimulation. The experimental flow is shown in Figure 1.

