### taVNS and sham stimulations

The stimulation is provided by the SDZ-IIB electronic stimulator (Suzhou Medical Supplies Factory), which stably delivers continuous wave taVNS in the range of 1–100 Hz. In taVNS studies, the stimulation current intensity is commonly set according to the patient’s perception threshold, usually at 1–1.5 mA, depending on the patient’s tolerance (Badran et al., 2018). Based on previous experimental studies, we consider that the absence of a significant increase in heart rate, decrease in blood pressure, and painful expressions during stimulation mean that the patient tolerates the stimulation. Two silicone tips of the SDZ-IIB electronic stimulator are placed in the patient’s ear cavity and ear canal, and each patient receives five different frequencies of taVNS and a sham stimulus in a randomized order. The technical parameters of the sham stimulation are identical, but no current is passed through.

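### The primary index, before–after change in CRS-R, names no adjustment for the pre-session score; adding it would usually sharpen the frequency-versus-sham comparisons at no extra data cost

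*Protocol article*

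**What the plan says.** The last paragraph of the Introduction sets the primary measure: "Changes in CRS-R scores will be used as the primary evaluation index". Under Procedures, "CRS-R scores will be recorded before and after each stimulation", so every session yields a pre/post pair. The design is a within-patient crossover: under taVNS and sham stimulations, "each patient receives five different frequencies of taVNS and a sham stimulus in a randomized order", and Procedures adds "where the order of stimulation is completely randomized". Procedures also sets the sample size and status: "This is a prospective exploratory trial including 15 MCS patients". Sessions are at least 48 h apart.

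The Statistical analysis section covers software, the third-party analyst and the handling of missing values. It names no model or test for comparing the frequencies, and no covariate.

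**The concern.** In this crossover each patient serves as his or her own control, so stable differences between patients drop out of any frequency-versus-sham contrast. What is left in a pre-session score is how that session's starting level differs from the patient's own average. Subtracting that deviation in full is right only if it carries over one-for-one to the post score. If the carry-over is partial, subtraction over-corrects: a session that happens to start low tends to show a larger change, and one that starts high a smaller change.

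The trial aims to single out a best frequency among five with 15 patients. Avoidable noise in each contrast makes that ranking less reliable, and the covariate that would reduce it is already recorded at every session.

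**Working it through.** **Inputs from the article.** 15 patients; 6 conditions each (five frequencies plus sham), so up to 15 × 6 = 90 pre/post pairs; randomised order. The article gives no SD, correlation, alpha, power or sample-size calculation, so there is no stated figure to reproduce.

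**Assumptions.** Within-patient variance s² is the same before and after a session. The within-patient, session-level pre–post correlation is r, shown over a range.

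**Step 1: large-sample variance per session, patient effect removed.**
- Unadjusted change: 2s²(1 − r).
- Adjusted for the pre-session score: s²(1 − r²).
- Ratio, change to adjusted: 2(1 − r)/(1 − r²) = 2/(1 + r).
- Number of adjusted patients that match 15 unadjusted: 15(1 + r)/2.

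| r | change (s²) | adjusted (s²) | ratio | patients |
|---|---|---|---|---|
| 0.3 | 1.40 | 0.91 | 1.54 | 9.75 |
| 0.5 | 1.00 | 0.75 | 1.33 | 11.25 |
| 0.7 | 0.60 | 0.51 | 1.18 | 12.75 |
| 0.8 | 0.40 | 0.36 | 1.11 | 13.5 |
| 0.9 | 0.20 | 0.19 | 1.05 | 14.25 |

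Below r = 0.5, 2(1 − r) exceeds 1, so the change is noisier than the post score alone.

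**Step 2: detectable difference from sham.** Assume two-sided 0.05 and 80% power (multiplier 1.96 + 0.84 = 2.80) and 15 pairs, in units of s.
- r = 0.5: 2.80 × √(2 × 1.00/15) = 1.02 for change; 2.80 × √(2 × 0.75/15) = 0.89 adjusted.
- r = 0.7: 0.79 and 0.73.
- r = 0.9: 0.46 and 0.45.

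**Step 3: cost of estimating the slope in a small trial.**
- Joint model of 90 sessions: error df without the covariate are 90 − 15 (patients) − 5 (conditions) − 5 (sessions) = 65. The adjusted variance is inflated by (65 − 1)/(65 − 2) = 64/63 = 1.016. The adjusted-to-change ratio is therefore (64/63)(1 + r)/2: 0.76 at r = 0.5, 0.86 at 0.7 and 0.965 at 0.9. Break-even is r = 2 × 63/64 − 1 = 0.97. As r approaches 1 the loss tends to 1.6%, so it is at most about 2%.
- One frequency against sham on 15 paired differences: inflation (15 − 2)/(15 − 3) = 13/12 = 1.083; break-even r = 2 × 12/13 − 1 = 0.85; maximum loss about 8%.

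**Step 4: simulation.** 3,000 runs per value of r, 15 patients, six sessions in random order, no true effect.
- Joint model: the ratio of mean confidence-interval widths, adjusted to change, was 0.873, 0.929, 0.982 and 1.003 at r = 0.5, 0.7, 0.9 and 0.98. The squares of these are 0.76, 0.86, 0.96 and 1.01, in line with Step 3.
- Single pairs: the variance ratio was 0.98 at r = 0.8 and 1.05 at r = 0.9.
- Bias: the mean error of the change-score contrast was about 0.01 SD or less at every r, which is simulation noise.

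**Step 5: chance imbalance in starting level.** Between two conditions, the difference in mean pre-session score has SE √(2/15) = 0.37 s. The unadjusted change passes a fraction (1 − r) of it into the contrast, so a one-SE imbalance shifts the contrast by 0.18 s at r = 0.5 and 0.26 s at r = 0.3. This is not a second harm on top of Step 1. The excess variance there is (2/15)s²[2(1 − r) − (1 − r²)] = (2/15)s²(1 − r)², which is exactly the variance of that shift.

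**The case against.** The strongest reply is that the article names an index and not a model. It never says that the change will be analysed unadjusted, and the Statistical analysis section leaves the comparison open. A model of the change with the pre-session score as covariate satisfies the Introduction as written and gives the same condition contrast as modelling the post score with that covariate. Choice of covariates is often left to a fuller document. This stands: a reader might infer that the plan prescribes an unadjusted analysis, and the article does not say so. What remains is a recommendation about a stated primary index whose covariate is already collected.

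A reader might also infer that regression to the mean biases the comparison of frequencies. The design rules that out. Every patient receives all six conditions in randomised order, so regression to the mean falls equally, in expectation, on sham and on each frequency. Only chance imbalance in the realised sample is left, and Step 5 shows that this is the precision loss already counted. An uncontrolled pre-to-post change within one condition would be affected, but adjustment would not turn that into a treatment effect either.

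Finally, r may be high. Pre and post scores bracket a single 20-minute stimulation, and at least two physicians make each assessment, which may limit measurement error. At r = 0.9 the large-sample saving is only 5%. On the other side, the plan calls for at least two CRS-R assessments to establish a patient's state and anticipates sleepiness during EEG recording. Neither fixes r, and a slope of exactly 1 should not be taken for granted.

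**Conclusion.** The point holds as an efficiency improvement. An unadjusted change in CRS-R is a valid, unbiased basis for comparing each frequency with sham, but it is usually less precise than an analysis adjusted for the session's own pre-score. In large samples adjustment saves from 50% of the variance at r = 0 to 15% at r = 0.7, then 10% at 0.8 and 5% at 0.9.

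It would be too strong to say that adjustment always helps. That is a large-sample result. With these numbers it reverses above r of about 0.97 in the joint model (loss at most about 2%) and above about 0.85 when one frequency is compared with sham on 15 differences alone (loss at most about 8%). This is why the joint model is the better vehicle.

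The sizes rest on equal pre and post within-patient variances and on an assumed r. The trial is exploratory and makes no power claim that a change score would break, so nothing here invalidates the design.

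**What to change.** State in the analysis text that the primary comparison is each frequency minus sham, estimated from one linear mixed model of all sessions, with:
- outcome: CRS-R change or post-session CRS-R (with the pre-score in the model, both give the same contrasts);
- fixed effects: condition (six levels including sham), session number, and the pre-session score entered as two terms, the patient's mean pre-score and the session's deviation from it;
- random effect: patient.

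The two-term split matters. With a random patient effect and a single pre-score term, the slope would mix between-patient and within-patient relations, and only the within-patient slope is relevant to these contrasts.

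Keep the unadjusted change per condition as a descriptive summary. The cost is a few lines of analysis wording, with no additional assessments, sessions or patients. The choice should be fixed before unblinding.

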## Methods

### Patients

We plan to recruit 15 patients diagnosed with MCS at the Department of Neurosurgery, Beijing Tiantan Hospital, Capital Medical University. Patients will be assessed for inclusion criteria at admission by the principal investigator and screened according to exclusion criteria. Patients’ current state of consciousness will be determined using at least two CRS-R assessments. Inclusion and exclusion criteria are shown in Table 1.

**TABLE 1 T1:** Study inclusion and exclusion criteria.

Inclusion criteria	Exclusion criteria
(1) Meeting the diagnostic criteria for MCS	(1) Open craniotomy
(2) Aged between 19 and 65 years old	(2) Brainstem injury
(3) Responding to auditory stimuli	(3) Pacemaker
(4) 3–12 months after injury	(4) Pregnant women
(5) Skull defect area less than one-third	(5) Metallic brain implants
(6) Family members agreed to sign an informed consent form	(6) Serious medical conditions that may affect clinical diagnosis or EEG activity

### Procedures

The pilot study will begin as early as day 30 after the patient’s injury and will be completed within 1 year of the injury. Written informed consent will be obtained from the patient’s legal representative following an open discussion of the study objectives, methods, and potential risks. The patient’s legal representative will be informed that the patient’s legal representative has the right to ask the patient to withdraw from the study at any time during the course of the study and that each party will retain a copy of the signed informed consent form.

This is a prospective exploratory trial including 15 MCS patients, each receiving a total of five different frequencies of taVNS (1, 10, 25, 50, and 100 Hz) and a sham stimulus as a blank control for 20 min, where the order of stimulation is completely randomized. We chose these five frequencies to span the range used in previous taVNS studies, including our own. Patient’s CRS-R scores will be recorded before and after each stimulation. Each CRS-R score will be performed by no fewer than two physicians with extensive clinical experience. Also, by using a bedside 32-channel EEG (Nicolet EEG V32, Natus Neurology, USA), a 10-min resting EEG will be recorded before and after each stimulation, respectively. The interval between stimulations will be at least 48 h. SDZ-IIB electronic stimulator (Suzhou Medical Supplies Factory) will be used to provide stimulation. The experimental flow is shown in Figure 1.

**FIGURE 1 F1:**
[figure not shown]
Single stimulation process and parameters used for stimulation.

Consistent with our previous experiments, a pair of identical-looking clips will be placed on both ears. The clips are designed with three carbon-impregnated silicone tips, one of which serves as the common end for supporting the posterior surface of the auricle, and the other two tips are designed to stimulate two skin surface points, one in the outer ear and the other in the navicular bone, with the two silicone tips at the outer ear point placed in the Cymba conchae and the Cavum conchae, respectively, as these are the two areas where the vagus nerve is most densely distributed in the ear. As shown in Figure 2, the SDZ-IIB electronic stimulator provides electrical pulses and continuous waves with a current of 1–1.5 mA. Real stimuli with frequencies of 1, 10, 25, 50, and 100 Hz are used on five occasions throughout the experiment, while a sham stimulus with the turned-off stimulator will be used on one occasion.

**FIGURE 2 F2:**
[figure not shown]
Stimulation sites of taVNS.

### Assignment of interventions: Blinding

Throughout the trial, subjects and their legal representatives, caregivers on the medical team, and all researchers involved in patient assessment and statistical analysis will be blinded to the assignment of the intervention. During the trial, six envelopes of the same color, texture, and size will be placed in a box that will only be opened on one side. The investigator will randomly select an envelope and give it to a clinically experienced physician who will adjust the stimulation parameters for the patient according to the envelope instructions, and the extracted envelope will not be placed back in the box. This physician will not have any communication (including written, email, or verbal communication) with the investigator, the subject and his or her legal representative, the entire medical team, or the research staff involved in patient assessment and statistical analysis.

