In contrast to the previous study, we will eliminate the sparse wave treatment and replace it with a continuous wave treatment. This is because the experiment needs to control for a single variable frequency. Based on previous reports in the literature, we will use 1 Hz, 10 Hz, 25 Hz, 100 Hz, and sham stimuli as controls and 50 Hz as a supplement considering the large gap between the 25 and 100 Hz ranges. According to the existing literature (Sun et al., 2021), the retention effect of taVNS on the EEG lasts for about 1 h. Therefore, we will set a 48-h interval, i.e., a 48-h interval before the two stimuli, to ensure that the next stimulus does not receive the effects of the previous one.

In this study, we propose investigating the changes in behavior and brain function induced by taVNS in DOC patients using CRS-R and EEG measurements. In addition, the relative power of the oscillations will be used to assess the effects of different frequencies of taVNS on the EEG of MCS patients. Based on this, we will attempt to initially explore the selection of the optimal stimulation frequency parameters of taVNS for DOC patients through this experiment and to lay the foundation for subsequent experimental studies.

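### Drawing each patient's session order without restriction leaves avoidable chance imbalance over session number and preceding condition in 15 patients; a pre-generated Williams-based list would remove most of it cheaply

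*Protocol article*

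**What the plan says.** The Procedures section of the protocol article describes a within-patient comparison of 1, 10, 25, 50 and 100 Hz and sham, "where the order of stimulation is completely randomized". The section on taVNS and sham stimulations repeats that "each patient receives five different frequencies of taVNS and a sham stimulus in a randomized order".

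The mechanism is in the section on blinding: "six envelopes of the same color, texture, and size will be placed in a box". Then, "The investigator will randomly select an envelope and give it to a clinically experienced physician", and "the extracted envelope will not be placed back in the box". The article does not say that the box is refilled for each patient, but this follows from every patient receiving all six conditions. Each order is therefore an unrestricted random permutation of six conditions, drawn separately for each patient. Nothing in the text balances conditions over sessions or over what came before.

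The sample size is in the Patients section: "We plan to recruit 15 patients diagnosed with MCS". Two features of the design limit order effects. CRS-R and EEG are measured before and after every session, and change in CRS-R is the primary index. There is also a washout: "The interval between stimulations will be at least 48 h". The Discussion justifies that interval by a literature finding that "the retention effect of taVNS on the EEG lasts for about 1 h".

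**The concern.** The trial sets out to pick a best frequency among five, using one session per frequency in each of 15 patients. In a crossover with six periods, the realized orders determine how cleanly a frequency can be separated from the session in which it was given and from the condition before it. Unrestricted permutations balance these only in expectation, and 15 patients are too few for that to give close balance in the trial actually run.

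If the response to a session changes as sessions go by, a frequency that happened to fall early or late would look better or worse for that reason. If the analysis adjusts for session, the price is paid in precision instead. An analysis plan can add such terms, but it cannot restore balance once the orders have been drawn.

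**Working it through.** The article gives no balance or power figure, so there is nothing to reproduce. The check needs only the design.

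**Inputs.** 15 patients (Patients section). Six conditions, each once per patient (Procedures; taVNS and sham stimulations). Unrestricted draw without replacement (blinding section).

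**Empty cells.** A given frequency falls in a given session with probability 1/6 per patient. A given condition directly precedes a given other one with probability 5 × 1/30 = 1/6. Over 15 patients, the probability that a given cell or ordered pair never occurs is (5/6)^15 = 0.065. The expected numbers are:
- frequency-by-session cells: 36 × 0.065 = 2.3 empty, against an expected count of 15/6 = 2.5 per cell;
- ordered preceding/current pairs: 30 × 0.065 = 1.9 absent, against an expected count of 15 × 5/30 = 2.5 per pair.

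**Mean session number.** A position uniform on 1 to 6 has variance 35/12, and two conditions in the same patient have covariance −7/12. The difference in position therefore has variance 2 × 35/12 + 2 × 7/12 = 7 per patient. Over 15 patients, the SD of the difference in mean session number between two conditions is √(7/15) = 0.68 session.

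**Simulation.** I compared 15 independent permutations (20,000 simulated trials for the counts) with Williams-based lists of two full squares plus three distinct rows. Variances come from least squares with patient, session and frequency effects, with and without a term for the preceding condition. They are expressed relative to the orthogonal value 2/15, in units of the residual variance.

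| | Unrestricted draw | Williams-based, 15 patients |
|---|---|---|
| Empty frequency-by-session cells (of 36) | 2.3; at least one in 92% of trials | 0 |
| Absent ordered pairs (of 30) | 1.9; at least one in 88% of trials | 0 |
| Count per cell and per pair | uneven, often 0; fullest session cell averages 5.9 | 2 to 3 |
| Gap in mean session number, frequency furthest from sham | 1.0 (95th percentile 1.7) | 0.3 (maximum 0.6) |
| Variance of frequency minus sham, session-adjusted | 1.08 (worst contrast 1.13) | 1.01 |
| Same, plus preceding condition | 1.22 (worst contrast 1.32) | 1.05 |

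None of the 20,000 unrestricted trials reached the best attainable spread of 2 to 3 in every frequency-by-session cell.

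**What is avoidable.** With session adjustment, 1.08/1.01 = 1.07, so standard errors are √1.07 = 1.03 times as wide, and the loss is worth 15 − 15/1.07 ≈ 1 patient. With the preceding condition as well, 1.22/1.05 = 1.16, standard errors are √1.16 = 1.08 times as wide, and the loss is worth 15 − 15/1.16 ≈ 2 patients.

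**If session is ignored.** The article gives no figure for a trend, so assume that the before-to-after response shifts by b residual SDs per session. An unadjusted difference between two conditions is then off by a random amount with SD 0.68b, against a standard error of √(2/15) = 0.365. The added variance is (7/15)b² ÷ (2/15) = 3.5b². That is 3.5% at b = 0.1 and 14% at b = 0.2, and nothing if the response is stable.

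**The case against.** The strongest reply is that nothing here is wrong. Every patient receives every condition in random order, so frequency contrasts are unbiased over the randomization. A reader might infer from the empty cells that the contrasts are biased, or cannot be estimated. The article does not support either reading. The imbalance is a matter of chance in the one trial run, and in an additive model all contrasts remain estimable with empty cells. Variance is the measure of harm, and it is small. This part stands in full.

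The before-and-after measurement also answers much of the worry about recovery and repeated testing. Steady drift in CRS-R level between sessions is differenced out. Only a change over sessions in the response to a session, such as habituation or practice, would matter, and the article gives no figure for one. This stands too.

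The washout is at least 48 hours against a cited retention of about one hour. It is tempting to say that carry-over makes the preceding condition matter, but the article does not show this. Equally, the retention figure concerns EEG, and none is given for CRS-R, the primary index. So carry-over is not excluded for the primary outcome, and the 22% figure applies only if a term for it is fitted.

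A reader might also infer that orders are improvised at the bedside and cannot be audited. The text does not say where the draw takes place. A draw can be logged, and a condensed article commonly leaves allocation records to the full protocol. Session terms in the analysis likewise belong to a plan that is not shown, and their absence is not counted here.

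What the objection does not meet is that the order rule is stated explicitly, and that a better one costs almost nothing.

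**Conclusion.** The point holds as a cheap improvement in efficiency and balance, not as an error in the randomization. Imbalance is almost certain under the stated draw, and its cost is modest: about 8% in variance with session adjustment against 1%, and about 22% against 5% if the preceding condition is modelled as well. If session is left out of the analysis, the consequence is chance confounding, and only to the extent that the before-to-after CRS-R response changes over sessions. The part about the preceding condition depends on CRS-R effects outlasting 48 hours, on which the article is silent.

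The figures assume that the box is refilled for each patient, that all 15 patients complete six sessions, and that residual variance is constant in an additive model.

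**What to change.** Generate the 15 sequences before recruitment from Williams squares of order 6: two complete squares (12 patients) plus three distinct rows of a third. Assign conditions to the square's labels at random, and allocate sequences to patients in random order. Put each patient's six conditions in sequentially numbered envelopes, opened in that order by the physician who sets the stimulator.

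The third-party statistical centre named in the Statistical analysis section can prepare the list. Because the blinding section keeps those doing the statistical analysis blinded, the person who makes the list should not be the one who analyses the data.

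This gives 2 to 3 occurrences of every frequency in every session and of every ordered pair. Exact balance would need a multiple of six patients (12 or 18), and the change does not require that. Session number is then a natural factor in the model, with the preceding condition as a sensitivity check.

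The cost is about an hour of preparation. Patient numbers, visits, the interval between sessions and the blinding arrangement stay as they are.
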